
#### **10.2.2 EGFR mutation testing at screening**

The tumor tissue samples used for testing can be derived from primary tumors or metastatic tumors. The tumor biopsy samples used for screening cannot be derived from tumor lesions that have received local treatment such as irradiation. The biopsy samples may not be subject to the 28-day screening window (test reports issued within 3 months before screening are deemed valid). If the biopsy sample is from Stage IV tumor tissue, a repeated biopsy is not required. Patients who fail screening due to the first tumor tissue testing may be re-screened if the investigator believes that the failure may be related to sample collection and another biopsy sampling is required. Patients must sign the informed consent form again before re-screening. Upon re-screening, the laboratory tests and imaging examinations are not required to be repeated if the previous tests/examinations are within the time window, and re-testing/re-examination is required if the previous ones are beyond the time window. In case the tumor tissue is not accessible by biopsy and the sample submitted is a blood sample, if the test result is negative for EGFR mutation, it is recommended to use a tumor tissue sample for a second testing. If a tumor tissue sample is not available, the subject will not be enrolled.

#### **10.3 Safety Evaluation**

Occurrence of AEs; occurrence of SAEs; proportion of patients withdrawn due to AEs; changes in laboratory tests (blood biochemistry, hematology, and urinalysis); changes in vital signs, physical examination, body weight, ECG, LVEF, ECOG score, and ophthalmological examination.

#### **10.4 Sampling and Testing Design**

##### **10.4.1 Exploratory sampling**

**Venous blood samples:** Samples need to be collected pre-administration on C1D1, within  $\pm 7$  days of administration on C2D1, and within 1 week after PD. Blood collection must be completed on the same day. See Table 5 for specific blood sampling time points.

**Table 5. Sampling plan**

| Time                                | Cycle 1 | Cycle 2 | PD   |
|-------------------------------------|---------|---------|------|
|                                     | D1      | D1      | D1-7 |
| Within 7 days before administration | ×       | ×       | ×    |

#### 10.4.3 Precautions for sampling

During the PK study, patients are prohibited from using any drugs or foods with a narrow therapeutic window that are strong inhibitors or inducers of CYP3A4 or sensitive substrates of CYP3A4 (e.g., pitaya, grapefruit, mango, and juice containing the above fruits). In addition, during this period, you should eat a light diet, avoid smoking and drinking, avoid tea, caffeinated and carbonated beverages, and avoid strenuous exercise.

### 10.5 Management of Biological Samples

#### 10.5.1 Sample collection volume

According to the study plan, for subjects undergoing the blood collection volume is 45 mL (Table 6) (C1D1, C2D1, within one week after PD).

**Table 6. Volume of blood collected**

| Visit         | Safety (mL) a | Gene mapping (mL) b |
|---------------|--------------------------|--------------------------------|
| C1D1          | 15                       | 8                              |
| C2D1          | 15                       |                                |
| D1–7 after PD | 15                       | 8                              |

Note: a, 6 mL for hematology and 9 mL for blood biochemistry; b, 8 mL for gene mapping sampling.

The total sample size required may be adjusted according to the protocol-specific procedures, changes, as well as methods established by the sample testing unit.

Laboratory safety assessments will be assessed using the respective established method in the laboratory of each study site. Therefore, the sample size required will vary from site to site.

#### 10.5.2 Destruction of biological samples

Biological samples will be retained for at most 3 years from the date of the last patient last visit (LPLV) and will be destroyed thereafter.

#### 10.5.3 Labeling and supervision of biological samples

Samples other than clinical test samples will be identified using the study number and subject screening number to ensure that the data of the samples can be linked to the clinical data. Samples may be destroyed in the event of patient's withdrawal of consent and reviewed by the regulatory authorities.

## 11.0 ADVERSE EVENTS AND MEDICAL MANAGEMENT

### 11.1 Adverse Events

#### 11.1.1 Definition of adverse event

An adverse event (AE) is an unexpected medical condition or worsening of a pre-existing medical condition after or during exposure to the investigational medicinal product, regardless of whether or not it has a causal relationship with the investigational medicinal product. An unexpected medical condition can be a symptom (e.g., nausea or chest pain), a sign (e.g., tachycardia or hepatomegaly), or an abnormality on examination (e.g., laboratory test or ECG).

AEs include but are not limited to the following conditions: 1) Worsening of pre-existing (before entering the clinical trial) medical conditions or diseases (including worsening of symptoms, signs, and laboratory abnormalities). 2) Any new AEs: any new untoward medical conditions (including symptoms, signs, and newly diagnosed diseases). 3) Clinically significant abnormal laboratory findings.

Exacerbation of the disease under study and its associated symptoms or signs are not considered AEs.

Any untoward clinical occurrence in a subject from signing the ICF to the first dose will be recorded as a medical history/concomitant disease, rather than an AE, unless any of the following conditions is met: injury/damage caused by any procedure related to the clinical laboratory tests; untoward occurrence caused by drug discontinuation related to the study protocol; untoward occurrence caused by drugs other than the investigational medicinal product which are taken as part of the treatment regimen. When a past medical history worsens during the study and is judged as an AE by the investigator, "Name of AE" should be filled in with "Aggravation of XX (name of past medical history)".

The start date of the AE is the date of past medical history aggravation, and the end date of the AE is the date of recovery to past medical history.

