#### 11.1.6 Adverse events based on examinations and tests

The results of protocol-specified laboratory tests and examinations, namely vital signs, ECG, and other safety assessments, will be summarized in the clinical study report. If these parameters suggest abnormalities compared with baseline, they will be reported as AEs only if they meet the criteria for SAEs, are judged by the investigator as clinically significant, or lead to discontinuation of study treatment (other than due to progressive disease).

When an abnormality in a laboratory value, vital sign, ECG, or other safety assessment is reported as an AE, the investigator should use the clinical term rather than the laboratory term whenever possible (e.g., anemia rather than decreased hemoglobin value).

For AEs of abnormalities in hematology, they should be reported specifically as "white blood cell count decreased", "neutrophil count decreased", "anemia", "platelet count decreased", etc., rather than using the AE name "myelosuppression". Reporting of percentage abnormality AEs (such as "neutrophil percentage decreased") is not required.

In case of abnormal liver enzymes, it should be reported by the name "XX enzyme increased/decreased", and ambiguous names such as "transaminases abnormal/increased/decreased" and "liver enzyme abnormal/increased/decreased" should not be used in reporting.

When changes occur in bilirubin-related indicators, "total bilirubin increased/decreased" and/or "direct bilirubin increased/decreased" and/or "indirect bilirubin increased/decreased" should be used in reporting. Ambiguous names such as "bilirubin abnormal/increased/decreased" and "blood bilirubin abnormal/increased/decreased" are not allowed for reporting.

Laboratory abnormalities due to unequivocal progressive disease should not be reported as AEs. Any new or

worsening clinically relevant abnormality in physical examination as compared to the baseline will be reported as an AE.

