#### 11.1.8 Progressive disease

Progressive disease and its associated signs and symptoms are considered an exacerbation of the patient's condition, which may be an increase in the severity of the disease under study and/or an increase in the symptoms of the disease.

New lesions of the primary tumor under study or progression of existing metastases are considered progressive disease rather than an AE. Unequivocal progressive disease during the study will not be reported as an AE.

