#### **12.1.2 Progression-free survival (PFS)**

According to RECIST 1.1, PFS is defined as the time from the treatment initiation to the first occurrence of investigator-assessed objective tumor progression or death. In the absence of PD, even if the patient has discontinued aumolertinib treatment or received another anti-cancer treatment before PD, his/her imaging tumor evaluation should still be collected until RECIST-defined PD. Symptomatic deterioration is not considered a progression event.

Subjects who have not progressed or died at the time of analysis will be censored at the last date of their last RECIST assessment. If a subject has PD or dies after 2 or more missing visits, he/she will be censored at the last date of his/her last RECIST assessment. PFS-derived data are based on assessment date rather than visit date.

Systemic PFS and iPFS will be assessed separately:

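### The AE definition exempts any worsening of the study disease while other sections exempt only unequivocal progression, so disease-attributed events without documented progression can miss AE/SAE recording

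*Protocol*

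**What the plan says.** Section 11.1.1 defines an AE irrespective of causal relationship and lists, as item 1, the worsening of diseases present before the trial. It then carves out the study disease: "Exacerbation of the disease under study and its associated symptoms or signs are not considered AEs". No RECIST finding or degree of certainty is attached.

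Section 11.1.8 opens with "Progressive disease and its associated signs and symptoms are considered an exacerbation of the patient's condition" and continues: "which may be an increase in the severity of the disease under study and/or an increase in the symptoms of the disease". It closes more narrowly: "Unequivocal progressive disease during the study will not be reported as an AE".

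Section 11.1.6 takes the narrow line for laboratory values: "Laboratory abnormalities due to unequivocal progressive disease should not be reported as AEs". For examination findings it gives no disease exception: any new or "worsening clinically relevant abnormality in physical examination as compared to the baseline will be reported as an AE". Section 11.1.10 keeps a death out of SAE reporting only where it is clearly related to progression. Deaths not clearly due to progression, or of unknown cause, go in as SAEs within 24 hours.

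On the efficacy side, section 12.1.2 says "Symptomatic deterioration is not considered a progression event".

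**The concern.** The protocol contains two exemptions of different width. Under the wide one, the investigator's attribution to disease decides whether a record exists at all. Under the narrow one, progression must be unequivocal. With about 20 planned sites (synopsis), different sites can apply different sentences and each be compliant.

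The distinction matters in this trial. Every patient has brain metastases. Section 4.2.2 describes the drug as readily crossing the blood-brain barrier, and section 6.2 gives higher cerebrospinal fluid exposure as a reason for the raised dose. Safety at that dose is a secondary objective. Neurological symptoms are where drug effect and disease are hardest to separate, and a single-arm, open-label design has no control group in which differential attribution would show. An event never recorded cannot be recovered at the analysis stage.

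**Working it through.** The point is one of wording, and the plan gives no figure to reproduce. The rules side by side:

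| Section | What is exempt from AE/SAE reporting | Progression needed? |
|---|---|---|
| 11.1.1, after the list | Any exacerbation of the study disease, with symptoms and signs | No |
| 11.1.8, opening | Calls progression an exacerbation, possibly only more symptoms | Loosely |
| 11.1.8, last sentence | Unequivocal progression | Yes |
| 11.1.6, laboratory | Abnormalities due to unequivocal progression | Yes |
| 11.1.6, examination | Nothing | Not applicable |
| 11.1.10, deaths | Deaths clearly related to progression | Yes |

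**Tracing one case.** Take a patient with a new seizure between visits, attributed to the brain metastases, who is hospitalized and whose scan shows no progression.

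1. Under 11.1.1 it is an exacerbation of the study disease, so not an AE. Under the last sentence of 11.1.8 there is no unequivocal progression, so it is not exempt.
2. Section 11.1.2 defines an SAE as an AE meeting a seriousness criterion. If step 1 gives no AE, the hospitalization is not an SAE.
3. Section 11.1.11 requires SAEs to be reported within 24 hours whatever their causality. With no SAE, nothing triggers it.
4. Table 7 already offers categories for events unrelated or unlikely to be related to the drug. It is applied to AEs, so this event never reaches it.
5. Under 12.1.2 there is no PFS event at that time. Section 12.1.2 and Appendix D, section 4.5, keep the patient under RECIST assessment.
6. If the patient stops treatment, section 7.8.1 lists no reason for symptomatic deterioration, although Appendix D, section 4.5, foresees such patients. The summary of withdrawals due to AEs may miss the case too.

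**What else captures it.** Section 5.2.2 makes changes in physical examination, weight, vital signs and ECOG performance status safety endpoints, and section 12.3.3.5 cross-tabulates ECOG changes. These are scheduled summaries, every 8 weeks from cycle 2 under section 10. They carry no event term, CTCAE grade, seriousness or causality. The examination rule in 11.1.6 covers findings on examination, not a headache or seizure between visits. Section 10.1.6 also leaves the neurological examination out of the evaluation of later changes for clinical relevance.

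**Size.** With 63 treated patients, one omitted patient changes the incidence in an AE row by at most 1/63 = 1.6 percentage points. The change is zero if the patient already has another AE counted in that row. For the any-AE row this is likely: section 4.2.4 reports at least one AE in 93.9% of phase II subjects at 110 mg. Assuming that rate carries over and is independent of the omission, the expected effect per omitted patient is 1.6 × (1 − 0.939) = about 0.1 point. Rows for SAEs, Grade 3 or higher events and single preferred terms have more room to move, up to the 1.6-point limit.

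**The case against.** The strongest reply is that the sections can be read together. The specific provisions (11.1.6, the end of 11.1.8, 11.1.10) all point to the narrow rule, and 11.1.8 ties exacerbation to progression, so 11.1.1 could be shorthand. That is a fair account of the likely intent, but the text does not secure it. Section 11.1.8 says that progression counts as exacerbation, not that exacerbation requires progression, and it then allows progression to be only an increase in symptoms.

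Several stronger readings may tempt a reader and are not supported:

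- *That the worsening is counted in neither safety nor efficacy.* The safety endpoints outside AE reporting remain, and section 10.2.1 asks for extra imaging when signs or symptoms suggest it. Scanning continues to objective progression, and death from any cause is a PFS event. The gap concerns the AE/SAE record and PFS at that time.
- *That leaving symptomatic deterioration out of PFS is an error.* It agrees with the protocol's own RECIST appendix.
- *That item 1 of 11.1.1 contradicts the exemption.* A general rule followed by a carve-out is ordinary drafting.
- *That AE rates are biased by a stated number of points.* The documents give no rate of disease-attributed worsening without progression, so any such number would be a guess.

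**Conclusion.** The inconsistency holds and should be corrected. Section 11.1.1 and the opening of 11.1.8 allow a wider exemption than 11.1.6, the last sentence of 11.1.8 and 11.1.10. A compliant site can therefore leave disease-attributed events without documented progression out of the AE/SAE tables and 24-hour reporting before causality is assessed. Omission can only lower the reported rates, but its size is unknown beyond the ceiling of 1.6 points per patient, which assumes 63 treated patients. Whether any event is lost depends on which sentence sites follow. The primary endpoint, sample size, significance level and power are unaffected.

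**What to change.** Reconcile 11.1.1 and 11.1.8 with 11.1.6 under one rule: the exemption covers only signs and symptoms of unequivocal progression already documented when the event is reported. Record every other new or worsening sign, symptom or hospitalization as an AE, or as an SAE where a seriousness criterion is met, at awareness, with CTCAE grade and Table 7 causality. Attribution to disease then appears as a causality category instead of a missing record. If RECIST progression is documented later, flag the entry and keep it, so that the tables can be shown with and without flagged events.

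The rule should not wait for the next scan. Under section 10.2.1 that may be 8 weeks away, plus a 1-week window, while SAEs are due within 24 hours.

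The cost is a short wording change in two sections, a flag on the AE form, notice to sites, a few more AE entries and slightly less favourable reported AE rates.

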### 11.1.2 Definition of serious adverse event

A serious adverse event (SAE) is any AE that occurs during the study period and meets one or more of the following criteria:

- Results in death
  - Is life-threatening
  - Requires or prolongs hospitalization
  - Causes persistent or significant disability/incapacity or substantial disruption of the ability to conduct normal life functions
  - Result in congenital anomalies or birth defects
  - Other important medical events that require medical intervention to prevent one of the above outcomes
- \* "Hospitalization", as is required or prolonged due to diagnosis of an existing condition or elective surgery, due to efficacy evaluation for the study, or due to a specified course of treatment for the study target disease, will not be recorded and reported as an SAE.

Examples include but are not limited to the following, at the investigator's discretion:

- Rehabilitation facility
- Nursing home
- Routine emergency room admission
- Day surgery (e.g., outpatient/day/ambulatory surgery)
- Hospitalization for a pre-existing condition with no new AE or exacerbation of the pre-existing condition
- Hospitalization for administrative reasons (e.g., routine annual physical examination)
- Protocol-specified hospitalization during the clinical trial
- Elective hospitalization not related to worsening of AEs (e.g., elective cosmetic surgery)
- Hospital admission for blood product use only
- Social reasons (health care reimbursement)
- Hospitalizations and/or surgical procedures planned before or during the study for diseases existing before enrollment in the study are not considered SAEs as long as there is no unexpected worsening of the diseases (i.e., natural disease course) during the study

### 11.1.3 Documentation of adverse events

#### 11.1.3.1 Time period for collecting AEs and SAEs

In this study, AEs will be collected from the signing of the informed consent form until 28 days after treatment discontinuation. Any new or unresolved AEs observed during the 28-day follow-up should be followed up until recovery, stabilization, or until the subject is lost to follow-up. After the end of the safety follow-up, only treatment- or procedure-related SAEs will be collected.

#### 11.1.3.2 Follow-up of unresolved AEs

Any unresolved AE that is medically indicated at the patient's last study visit will be followed up by the investigator, but will not be further documented. The investigator reserves the right to collect information about ongoing AEs after the end of the study, if necessary. If the investigator learns of any new SAE at any time after a patient has completed the study and considers the event possibly related to aumolertinib, the marketing authorization holder (Jiangsu Hansoh Pharmaceutical Group Co., Ltd.) should be notified within 24 h of learning of the SAE.

#### 11.1.3.3 Key information on adverse events to be collected

Important information collected for each AE will include, but is not limited to, the following:

- Diagnosis/Description of the AE
- Start and end dates of the AE
- CTCAE grade
- Whether the AE is a serious adverse event
- Measures taken with the investigational medicinal product due to the AE
- Causal relationship determined by the investigator
- Treatment of the event (drug and/or non-drug therapies)
- Outcome

For SAEs, the following information will be collected:

- Event name (diagnosis)
- Description of the event
- Severity of the event
- Outcome of the event
- Start and end dates of the event
- Any relevant medical history, concomitant medications/treatments, and laboratory test results

- Treatment of the event (drug and non-drug therapies)
- Causal relationship determined by the investigator
- Cause of death (for a fatal event)

All AEs will be graded according to the grading criteria in the Common Terminology Criteria for Adverse Events (CTCAE) Version 5. For AEs not graded as per CTCAE, the recommendations in the CTCAE guidelines should be followed to convert mild, moderate, and severe events into CTCAE grades.

#### 11.1.4 Causal relationship determination

The investigator will assess the causality between the investigational medicinal product and each AE. The criteria for causality between AEs and the investigational medicinal product are shown in Table 7.

**Table 7. Criteria for causal relationship between adverse events and the investigational medicinal product**

| Causality          | Criteria                                                                                                                                                                                                                                                                                                                                    |
|--------------------|---------------------------------------------------------------------------------------------------------------------------------------------------------------------------------------------------------------------------------------------------------------------------------------------------------------------------------------------|
| Not related        | The AE is not related to the use of the investigational medicinal product. For example, no investigational medicinal product is used.                                                                                                                                                                                                       |
| Unlikely related   | There is no evidence to suggest a causal relationship between the occurrence of the event and the investigational medicinal product. The occurrence of the AE is more likely related to other factors, such as concomitant medications or diseases. However, a correlation between the two cannot be ruled out.                             |
| Possibly related   | The AE follows a reasonable temporal sequence from the administration of the investigational medicinal product, and may be caused by the investigational medicinal product, but can readily have been produced by other factors such as concomitant medications or diseases. No drug withdrawal is performed or the information is unclear. |
| Definitely related | The AE has been identified to follow a known response pattern to the drug and cannot be explained by other factors (such as concomitant medications and diseases). The time of onset strongly suggests a causality (e.g., dechallenge and rechallenge results).                                                                             |
| Indeterminable     | There is insufficient information to make a judgment on the causality between the event and the investigational medicinal product. The investigator may change her/his causality assessment and modify the corresponding AE/SAE report based on subsequent follow-up information.                                                           |

